### 2.2. Participants Recruitment and Sample Size

The research team will send an invitation to the intended users for this medical device, namely nurses from local tertiary hospitals to participate in the study. All interested nurses will be screened for eligibility criteria (Table 1). Regarding sample size, around 15–25 participants are usually considered to enroll in the usability tests, 15 being the acceptable minimum number according to the regulatory entities of the USA [26]. Although in the EU these parameters are not well-established, the U.S. Food and Drug Administration’s (FDA) orientation guidelines for medical devices highlight the need to balance the heterogeneity and homogeneity of the samples, reflecting as much as possible the target population [27]. For the usability tests with the double-chamber syringe, the AAMI/IEC/TIR 62366-2 was used to accomplish the sample size determination. According to that standard, there are diminishing returns on detecting new usability problems when sample size goes beyond 10 for each distinct user group. This is based on calculations determining cumulative probability of detecting a usability problem: R = 1 − (1 − P)^n^, where R equals the cumulative probability of detecting a usability problem, P equals the probability of a single test showing a usability problem, and n equals number of participants [20]. Therefore, 10 nurses will be enrolled in each arm (20 for each phase of this study), in a total of 40 participants in overall pre-clinical usability testing. The participants will not be compensated for participation.

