### 2.4. Randomization and Blinding

Eligible and consenting participants will be randomly allocated to one of two arms (Figure 1) for each phase of the study, using simple randomization (1:1 ratio). Random allocations through random number sequences will be computer-generated through an online registration system (Sealed Envelope^TM^, London, England). To ensure allocation concealment, the study staff will randomize each participant unknowingly and informed the principal investigator. Considering the specificities of this device, both of the two steps of the RCT will not be blinded, since it consists of the use of different devices to conduct the experiments of each allocated arm. Despite this, the participants will not be directly informed of their group allocation and will only be informed about the broad purposes of the research and the specific tasks they need to accomplish in the usability test.

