### 2.6. Interventions

This pre-clinical validation will be assessed through a two-arm parallel RCT in two phases (Figure 1), in which the nurses will be requested to perform intravenous drug administration per the allocated arm in the simulated setting. In order to ensure the standardized conditions for the procedure, the PIVC is already in place (being placed always by the same nurse of the research team). In the first phase (intra-subject analyses), the 20 nurses will perform the protocol using the two types of syringes, starting with the double-chamber syringe and, then, a standard syringe (arm A), or in reversed order (arm B). In the second phase (inter-subject analysis), another 20 nurses (without any previous information or contact with this double-chamber syringe) will be allocated to perform the protocol with a double-chamber syringe (arm A) or with standard syringes (arm B). The usability test session will be run as a single participant test, with each participant repeating the procedure three times, under external supervision. The procedure is divided in two main phases (drug preparation and drug administration), and tasks were defined in accordance to both study groups (Table 3 and Table 4). The procedure will be recorded by audio/video for posterior analyses. At the end of the usability tests, interviews/focus group with all participants will be conducted to collect detailed qualitative information about this new medical device.

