### 2.7. Outcomes

These usability tests are intended to measure primary (effectiveness, efficiency, and safety) and secondary outcomes (satisfaction and intention of use), ensuring that the medical device accomplishes the needed legal requirements before testing in real clinical settings. Specifically, in this pre-clinical study, the primary outcomes that will be measured are: (i) number of tasks and goals achieved; (ii) procedure execution time; and (iii) number, type, and intensity of errors (Table 5). These parameters will be extracted from the video recordings (usability tests) and compared to a detailed procedure checklist. The secondary outcomes will be assessed through the usability questionnaire and audio recordings from the individual interviews and focus group carried. As the participants perform each procedure three times (with the double-chamber syringe and standard syringes), the research team can also analyze their learning curve and training needs required to use this new medical device, along with the qualitative (interviews and focus group) and quantitative (usability questionnaire).

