### 2.8. Data Collection, Management, and Analysis

Study participants identification numbers (ID) will be used, and all data will be anonymized for subsequent analysis and reports/publications. Individual information to be collected includes demographic (gender, age), academic qualifications (degree), and professional data (clinical experience, work setting) of the nurses eligible to perform the usability tests. The names of the participants on the consent forms will be stored separately in locked cabinets accessible only by named personnel.

Statistical analysis of the collected data will be performed using the Statistical Package for the Social Sciences, version 24 (IBM SPSS Statistics 24; SPSS Inc., Chicago, IL, USA). Means, standard deviations, frequencies, and percentages will be used as descriptive statistics (or median values and interquartile ranges for skewed data). The outcomes in the two groups in each study phase will be examined to detect the effect of group allocation through inferential statistics (Student’s t-test for independent and paired samples, or non-parametric equivalents, Mann-Whitney U and Wilcoxon tests; X^2^ test or Fisher’s exact test), considering a statistical significance level of 0.05 (two-sided significance level of 5%). Qualitative content analysis will also be conducted after the transcription of the individual interviews and focus group.

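### For Phase 2 per-nurse yes/no outcomes, the plan's chi-square or Fisher choice amounts to Fisher in effect; Boschloo's exact test also holds 5% and has more power (low priority)

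*Protocol article*

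**What the plan says.** Section 2.8 lists the inferential tests. For categorical data these are the chi-square test or Fisher's "exact test), considering a statistical significance level of 0.05 (two-sided significance level of 5"%. It gives no rule for choosing between the two and does not mention a continuity correction.

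Section 2.2 sets the numbers: "10 nurses will be enrolled in each arm (20 for each phase of this study), in a total of 40 participants". Section 2.6 makes Phase 2 a between-nurse comparison: "In the second phase (inter-subject analysis), another 20 nurses" use either the double-chamber syringe or standard syringes. Section 2.4 allocates them "using simple randomization (1:1 ratio").

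The primary outcomes in section 2.7 include "iii) number, type, and intensity of errors (Table 5"). Table 5 lists error types, most of them marked as applying to both groups. A comparison of how many nurses made a given type of error is the natural place for the categorical tests, although the article does not define such a per-nurse endpoint in so many words.

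**The concern.** With about 10 nurses per arm a 2×2 table has few possible outcomes, and the two named tests behave differently. Fisher's test, which conditions on the total number of nurses who err, can work far below its nominal level. The uncorrected chi-square test relies on a large-sample approximation and can work above it. The comparison has few nurses to begin with, so a needlessly conservative test makes it more likely that a real excess of errors with one syringe is reported as non-significant. Because errors are the safety part of the primary outcome, that is a costly kind of mistake.

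**Working it through.** **Inputs from the article.** Two-sided level 0.05 and the two named tests (section 2.8); 10 nurses per arm in Phase 2 (sections 2.2 and 2.6); simple 1:1 randomization (section 2.4). The article states no power, effect size or event rate, so there is no figure of that kind to reproduce. Its sample size comes from the problem-detection formula R = 1 − (1 − P)^n.

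**Assumptions made here.** Each nurse contributes one yes/no value. Event rates are illustrative.

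**Step 1: one table by hand, 0/10 v 4/10.**
- Fisher, two-sided: 2 × C(10,4)/C(20,4) = 2 × 210/4845 = 0.087.
- Uncorrected chi-square: 20 × (0×6 − 10×4)² / (10×10×4×16) = 20 × 1600/6400 = 5.00, p = 0.025.
- Yates-corrected: 20 × (40 − 10)² / 6400 = 2.81, p = 0.094.
- Boschloo, the largest probability over a common rate of a table with a Fisher p-value at least as small: 0.042.

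Likewise 1/10 v 6/10 gives Fisher 0.057, chi-square 0.019 and Boschloo 0.023; 2/10 v 7/10 gives 0.070, 0.025 and 0.041.

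**Step 2: all 121 tables at 10:10.** Fisher and uncorrected chi-square differ at 0.05 in 12 tables. The smallest expected count in those tables is 2.0, 3.5 or 4.5, so the usual rule (Fisher if any expected count is below 5) sends all 12 to Fisher. At 10:10 the rule reaches chi-square only when exactly 10 of 20 nurses err, and there the two tests agree. Yates-corrected chi-square rejects in exactly the same tables as Fisher at 10:10. At 9:11, 8:12 and 7:13 the expected-count rule again gives the same verdicts as Fisher.

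**Step 3: true size.** For a rejection region R, size = max over p of Σ over (a,b) in R of Bin(a; n1, p) × Bin(b; n2, p).

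| Split | Fisher | Uncorrected chi-square | Boschloo |
|---|---|---|---|
| 10:10 | 1.3% | 4.2% | 4.2% |
| 9:11 | 2.8% | 5.7% | 4.2% |
| 8:12 | 2.3% | 5.9% | 4.3% |
| 7:13 | 2.1% | 5.9% | 4.2% |

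At 10:10 Boschloo and uncorrected chi-square have the same rejection region. At every split shown, Boschloo rejects whenever Fisher does.

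**Step 4: how likely an unequal split is.** If 20 nurses are allocated by unrestricted simple randomization, P(10:10) = C(20,10)/2^20 = 184,756/1,048,576 = 17.6%. If enrolment is held to 10 per arm, the 10:10 row applies.

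**Step 5: power.** The sum is as in Step 3, with two different rates.

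| Assumed rates | Fisher, 10:10 | Boschloo, 10:10 | Gain (points) |
|---|---|---|---|
| 10% v 30% | 5.7% | 14.3% | 9 |
| 10% v 50% | 29.5% | 47.1% | 18 |
| 10% v 60% | 47.4% | 65.9% | 19 |
| 20% v 70% | 42.6% | 62.2% | 20 |

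At 9:11, 8:12 and 7:13, with either arm the larger, the gain for the same four pairs runs from about 0 to about 16 points. Averaged over simple-randomization splits from 5:15 to 15:5 (98.8% of the probability), Fisher v Boschloo is 0.36 v 0.45 for 10% v 50%, 0.55 v 0.64 for 10% v 60%, and 0.48 v 0.60 for 20% v 70%: gains of about 9, 9 and 13 points.

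**The case against.** The strongest reply is that nothing in section 2.8 is wrong. Both tests are standard, 5% is a nominal threshold, and an exact test that works below its threshold still controls type I error. That stands: a reader might take a true size of 1.3% against a stated 5% for a discrepancy, and it is not one.

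A reader might also infer that leaving the choice open lets the analyst pick the verdict. The article does not support that as a defect. The selection rule is a detail that an article commonly leaves to the full protocol or analysis plan, and at 10:10 both the usual expected-count rule and the Yates correction lead to Fisher's verdict. Opposite verdicts need uncorrected chi-square used against the usual rule, and then arise in only 12 of 121 tables.

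A third tempting reading is that Fisher costs about 20 points of power. That needs an exact 10:10 split and rates such as 20% v 70%, which the article does not give; averaged over splits the loss is smaller.

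It is also fair to say that the study is sized for detecting usability problems, not for power, and that the primary outcomes are mainly counts and time. Each nurse repeats the procedure three times, so a yes/no value per nurse has to be derived. This limits the reach of the point. It does not remove it, because section 2.8 does name tests for categorical comparisons, and following the usual rule with either of them means accepting Fisher's conservatism.

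**Conclusion.** The point holds as a low-priority improvement. For independent-group, per-nurse yes/no outcomes in Phase 2, the named tests come down in practice to Fisher, with a true size of at most 1.3% at 10:10 and at most 2.1–2.8% at 9:11 to 7:13. Uncorrected chi-square is no safe substitute, since it exceeds 5% at those unequal splits. Boschloo keeps the level at every split examined and is never less powerful than Fisher there. The size figures depend only on the arm sizes. The power gain, about 9–20 points at 10:10 and 0–16 at the unequal splits, depends on assumed rates and on reducing each nurse's repeats to one yes/no value. The within-nurse comparisons of Phase 1 and the time and count outcomes are outside the point.

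**What to change.** In section 2.8, for independent-group per-nurse yes/no outcomes in Phase 2, replace the choice between chi-square and Fisher with one named test: Boschloo's unconditional exact test at two-sided 5%, reported with the risk difference and an exact 95% confidence interval. The same sentence should say how a nurse's three repeats become one yes/no value, for example error in any repeat.

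The cost is a sentence or two and no extra participants. The one drawback is that the test may have to be run in a free package if SPSS 24, the named software, does not offer it.

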### 2.9. Ethical Considerations

This double-chamber syringe is a new medical device that is currently under development. Due to this, this pre-clinical protocol was defined according to the legal requirements of the European Union [15], and the ISO norms related to ergonomics and usability assessment of MDs [16,17,18,19,20,21]. The study protocol and all the templates that will be used in usability tests were reviewed and approved by the Ethics Committee of the Health Sciences Research Unit: Nursing of the Nursing School of Coimbra (Number P608-8/2019).

The eligible nurses will receive written and oral information about the study and written informed consent and a non-disclosure agreement (NDA) will be requested to the nurses that are willing to participate. As previously stated, participants will be assigned to an ID number, which will be used in all data collection instruments. Personal information will be separated from the main data collected and will not be shared. All the documentation related to the study will be saved in locked cabinets only accessible by the study staff. All collected data will be used exclusively for this study, and the confidentiality of participants will always be maintained. Participants have the right to withdraw from the study at any time, as established by national legislation, without any consequences for them. In this case, information related to the reason of withdrawing will be collected.

### 2.10. Dissemination

Due to the absence of specific guidelines for pre-clinical studies with medical devices, upon completion of the usability tests in both phases, the Consolidated Standards of Reporting Trials guidelines (CONSORT 2010) [28,29] will be used to report the data obtained, with adjustments for health care simulation research specificities [30,31]. All the data will not be publicly available but will be accessible from the principal investigator on reasonable request. The pre-clinical research results will be disseminated open-access, peer-reviewed journals and national and international scientific meetings. Authorship will be considered according to the recommendations of the International Committee of Medical Journal Editors [33], regarding the contributions to the design, conduct, interpretation, and reporting the pre-clinical data [34].

## 3. Results

Pre-clinical studies on this new double-chamber syringe will be initiated soon, with the recruitment of eligible nurses to perform the usability tests in a simulation lab. The clinical trial is already registered at ClinicalTrials.gov (NCT04046770). After the pre-clinical studies, all legal documentation will be submitted to Portuguese legal entities to implement the clinical trial in real hospital setting.

## 4. Discussion

Peripheral intravenous catheterization is the most frequent invasive procedure performed in nursing clinical practice and enables the intravenous administration of fluids directly on the bloodstream [35,36]. In this clinical practice, there is a wide range of complications that can impact patient´s safety [37,38], and the flushing procedure is recommended to prevent major mechanical, vascular, or infectious complications [39,40]. In several international guidelines on infusion nursing flushing is also mentioned to assess the catheter patency previously to drug administration and to clean the catheter after the drug delivery [2,3,41]. The main purpose of flushing is to maintain PIVC patency by preventing internal luminal occlusion, reducing the build-up of blood or other products on the catheter internal surface, also preventing interaction between incompatible fluids or drugs [5,42,43].

Currently, this process requires at least the use of two different syringes (one for drug and one for flush solution). The double-chamber syringe will enable nurses to perform the recommended pre- and post-PIVC flush during intravenous therapy administration, reducing the catheter manipulations and subsequent possible complications. Moreover, the authors expect that this new medical device can assist healthcare organizations in providing sustainable care, by reducing the number of syringes needed for such a recurrent procedure.

The development of this new device has followed the UCD method, widely recognized as the gold standard to address the real needs of the targeted end-users. Given its potential impact on patients’ safety and well-being, medical devices require safety and usability testing before market distribution [25]. Usability tests are universally accepted as essential requirements for the validation of devices’ effectiveness, efficiency, safety, and satisfaction parameters [24]. Although medical devices’ regulation is not yet unvarying, the IMDRF directives, along with the EUnetHTA JA2 2015, transposed some methods from pharmaceuticals regulation (e.g., effectiveness of the new medical device compared with the standard method/device) and provided international guidance [13,44,45] that were used to define this pre-clinical study protocol.

## 5. Conclusions

Following international legal directives, a protocol for pre-clinical usability tests was delineated, comparing the standard syringes currently used in clinical practice and the new double-chamber syringe. The authors expect that the development of this new medical device (double-chamber syringe) will improve nursing practice by enhancing adherence to quality and safety recommendations in the administration of intravenous therapy.

## Figures and Tables

**Figure 1 ijerph-17-08376-f001:**
[figure not shown]
Flowchart of the two-arm parallel randomized controlled trial (RCT).

**Figure 2 ijerph-17-08376-f002:**
[figure not shown]
Simulation environment in nursing laboratory for usability tests, with (**a**) the material available for the participants and (**b**) the training arm kit with an inserted peripheral intravenous catheter (PIVC) to simulate intravenous drug administration and flushing.

**Table 1 ijerph-17-08376-t001:** Eligibility criteria for participants.

Inclusion Criteria	Exclusion Criteria
✓ Nurses	✓ Other health professionals
✓ Minimum academic qualifications of a bachelor degree	✓ Any previous contact with the device (knowledge and/or manipulation)
✓ Experience on intravenous drug administration	✓ Individuals who have a financial relationship with the device manufacturer and/or distributor

**Table 2 ijerph-17-08376-t002:** Interviews and focus groups guidelines.

Steps	Duration (Min)	Purposes
Introduction	5 min	✓ Presentation of the main objective for the interview/focus group.
Discussion	30 min	✓ Discussion on the main advantages and limitations of the new double-chamber syringe, comparing them with the standard syringes (“We would like you to summarize your experience with this new medical device, the Duo Syringe. We want you to help us to identify its advantages and potential, as well as any limitations or difficulties that you have identified when using it in these usability tests”). ✓ The participants are also asked to answer the usability questionnaire.
Conclusion	5 min	✓ Show appreciation for participation and obtain main (anonymous) information to characterize the group.

**Table 3 ijerph-17-08376-t003:** Procedures to be accomplished by the study participants: drug preparation.

	Standard Syringe	Double-Chamber Syringe
Phase 1 (Drug Preparation)	Determine the total drug dose to be administered according to chart prescription. Check the drug ampule for intactness, cloudiness, particles, and color. Gently flick or tap the top of the ampule to remove medication trapped in the top of the ampule. Wrap a 2 in. × 2 in. gauze pad around the neck of the ampule, snap the top off, breaking it. Discard the top in a sharps container. Attach a 18G filter needle to a 10 mL syringe. Withdraw the medication from the ampule. Hold the syringe vertically and draw 0.2 mL of air into the syringe. Remove the filter needle and attach a blunt 18G needle. Eject the 0.2 mL of air and read the dose. Attach a blunt 18G needle to a 10 mL syringe. Remove the neck of a plastic ampule containing 0.9% normal saline for catheter flush. Discard the neck. Withdraw 10 mL of normal saline from the ampule. Hold the syringe vertically and draw 0.2 mL of air into the syringe. Eject the 0.2 mL of air and read the dose. Label both syringes. Prepare a tray with the syringes, pair of clean gloves, sterile gauze, and a 2% chlorhexidine gluconate in 70% isopropyl alcohol spray.	Determine the total drug dose to be administered according to chart prescription. Attach a 18G filter needle to the syringe. Remove the neck of a plastic ampule containing 0.9% normal saline for catheter flush. Discard the neck. Withdraw 10 mL of normal saline from the ampule to the white plunger chamber. Hold the syringe vertically and draw 0.2 mL of air into the syringe. Eject the 0.2 mL of air and read the dose. Check the drug ampule for intactness, cloudiness, particles, and color. Gently flick or tap the top of the ampule to remove medication trapped in the top of the ampule. Wrap a 2 in. × 2 in. gauze pad around the neck of the ampule, snap the top off, breaking it. Discard the top in a sharps container. Withdraw the medication from the ampule to the blue plunger chamber. Hold the syringe vertically and draw 0.2 mL of air into the syringe. Remove the filter needle and attach a blunt 18G needle. Eject the 0.2 mL of air and read the dose. Label the syringe. Prepare a tray with the double-chamber syringe, pair of clean gloves, sterile gauze, and a 2% chlorhexidine gluconate in 70% isopropyl alcohol spray.

**Table 4 ijerph-17-08376-t004:** Procedures to be accomplished by the study participants: drug administration.

	Standard Syringe	Double-Chamber Syringe
Phase 2 (Drug administration)	Don clean gloves. Disinfect the catheter hub with the 2% chlorhexidine gluconate in 70% isopropyl alcohol spray. Place a sterile gauze below the catheter hub. Holding the flushing syringe, remove both the needle and the cap, and place them on a sterile surface. Insert the flush syringe into the catheter hub. Administer a 5 mL flush to clear the line with a push–pause technique. Continue to hold the catheter hub and apply positive pressure on the plunger. Remove the flush syringe, attach the needle, and place it on a sterile surface. Insert the drug syringe into the catheter hub. Administer the prescribed drug. Continue to hold the catheter hub and apply positive pressure on the plunger. Remove the drug syringe. Holding the flushing syringe, remove both the needle and the cap. Insert the flush syringe into the catheter hub. Administer a 5 mL flush to clear the line with a push–pause technique. Remove the flush syringe. Remove the sterile gauze. Leave the patient room.	Don clean gloves. Disinfect the catheter hub with the 2% chlorhexidine gluconate in 70% isopropyl alcohol spray. Place a sterile gauze below the catheter hub. Holding the flushing syringe, remove both the needle and the cap, and place them on a sterile surface. Insert the double-change syringe into the catheter hub. Administer a 5 mL flush to clear it with a push–pause technique. Continue to hold the catheter hub. Apply positive pressure on the drug chamber’s plunger and administer the prescribed dose. Continue to hold the catheter hub. Apply positive pressure on the flushing chamber’s plunger. Administer a 5 mL flush to clear the line with a push–pause technique. Remove the double-chamber syringe. Remove the sterile gauze. Leave the patient room.

**Table 5 ijerph-17-08376-t005:** Types of errors to be assessed during the study.

Phase 1 (Drug Preparation)	Phase 2 (Drug Administration)
✓ Defective connection of the needle to the syringe (both groups); ✓ Non-compliance with aseptic technique during needle connection (both groups); ✓ Incorrect drug dose or flushing volume after aspiration (in mL) (both groups); ✓ Non-compliance with aseptic technique during drug/flushing aspiration (both groups); ✓ Incorrect syringe labelling or label position (both groups); ✓ Wrong chamber aspiration sequence (double-chamber group); ✓ Aspiration of drug/flushing solution to the wrong chamber (double-chamber group); ✓ Chamber contamination (double-chamber group).	✓ Defective connection of the syringe to the catheter hub (both groups); ✓ Non-compliance with aseptic technique during syringe-to-hub connection (both groups); ✓ Incorrect administration of drug dose or flushing volume (in mL) (both groups); ✓ Non-compliance with aseptic technique during drug/flushing administration (both groups); ✓ Wrong administration sequence (both groups); ✓ Non-compliance with the push–pause technique during catheter flushing (both groups); ✓ Chamber contamination (double-chamber group); ✓ Catheter accidental removal (both groups).

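### One interview script about using the double-chamber syringe, with the usability questionnaire inside it, is applied to all nurses, including the Phase 2 arm that never uses the device

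*Protocol article*

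**What the plan says.** **Exposure.** Section 2.2 plans that "10 nurses will be enrolled in each arm (20 for each phase of this study), in a total of 40 participants". Under section 2.6, in Phase 1 "the 20 nurses will perform the protocol using the two types of syringes", in one order or the other. Phase 2 takes a fresh set of nurses, who must come to the test "without any previous information or contact with this double-chamber syringe". After randomisation each of them works with one type only: according to section 2.6 they "will be allocated to perform the protocol with a double-chamber syringe (arm A) or with standard syringes (arm B"). Table 1 also excludes nurses with "Any previous contact with the device (knowledge and/or manipulation").

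**Interviews.** Section 2.6 states that after the tests "interviews/focus group with all participants will be conducted to collect detailed qualitative information about this new medical device". The Abstract likewise places every participant in a final focus group. Table 2 contains one script, with no version by arm. It asks nurses to sum up their experience with the device and to "help us to identify its advantages and potential, as well as any limitations or difficulties that you have identified when using it".

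**Questionnaire.** In the same 30-minute Discussion step of Table 2, "The participants are also asked to answer the usability questionnaire". Section 2.5 describes the instrument as 42 seven-point items whose dimensions include satisfaction and intention to use. It does not name the syringe to be rated.

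**Use of the answers.** Section 2.7 takes both secondary outcomes, satisfaction and intention of use, from this questionnaire and from the interview and focus-group audio. Section 2.8 compares outcomes between the two groups within each phase at a two-sided 5% level.

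**The concern.** The script presupposes that the speaker has used the double-chamber syringe. A Phase 2 arm B nurse has not, and by the eligibility rules has no experience of it from elsewhere, so she cannot answer the question as put. The questionnaire that supplies the secondary outcomes sits in the same step, and no arm is exempted or given a different object to rate.

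Two things are at stake. The first is what the Phase 2 between-arm comparison of satisfaction and intention of use means, since that depends on what arm B was rating. The second is whether the ratings were made before or after the nurse was prompted about the new device's merits and drawbacks. The second point reaches all nurses, including those who did use the device. Ratings taken after a discussion cannot be repaired later.

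**Working it through.** **1. Planned head count.** Inputs are 10 per arm, two arms per phase and two phases (section 2.2). 10 × 2 × 2 = 40, which reproduces the article's total.

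**2. Who uses the double-chamber syringe (section 2.6).**

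| Group | Planned n | Double-chamber | Standard |
|---|---|---|---|
| Phase 1, both orders | 20 | yes | yes |
| Phase 2 arm A | 10 | yes | no |
| Phase 2 arm B | 10 | no | yes |

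Planned users of the device: 20 + 10 = 30. Planned non-users: 10, all in Phase 2, where they are 10/20 = 50% of the phase.

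Ten is a plan and not a guarantee. Section 2.4 uses simple 1:1 randomisation. With 20 nurses, the chance of exactly 10 per arm is C(20,10)/2^20 = 0.176, and arm B has between 6 and 14 nurses with probability 0.959.

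**3. What the Phase 2 comparison measures under each reading.** Write D for a rating of the double-chamber syringe and S for a rating of standard syringes.

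- *Arm B rates the double-chamber syringe.* The contrast is mean D among users minus mean D among non-users. Both terms concern the same device, so the contrast says nothing about double-chamber against standard syringes, and the arm B term is opinion without exposure.
- *Arm B rates standard syringes.* Let b_A and b_B be the mean shifts caused by answering within a step about the new device. The contrast is (D + b_A) − (S + b_B) = (D − S) + (b_A − b_B). The bias b_A − b_B is zero only if the discussion moves ratings of both syringes equally. Nothing in the article makes that likely, because the script concerns one of the two devices.

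The article gives no value for b_A, b_B or the gap between users and non-users, so neither the size nor the sign of the bias can be calculated.

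**4. Phase 1.** These nurses use both types, so the exposure problem does not arise. Only the timing of the questionnaire applies. The article does not say whether they complete it once or once per syringe type.

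**5. Primary outcomes.** Section 2.7 extracts task completion, time and errors from video against a checklist. None of these passes through Table 2.

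**The case against.** The other side has several fair points.

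- *The rated object is not stated.* Since section 2.8 compares groups within each phase, each arm may be meant to rate the syringe it used, in which case no non-user rates the new device. This stands as a possible reading, but it leaves the second problem in step 3 and does not mend the script.
- *Order and setting are not fixed.* Table 2 lists purposes within a step and covers individual interviews as well as focus groups. The article does not show that the questionnaire is answered in a group, nor strictly after the prompt. That also stands. What is fixed is that both fall in one step, with nothing requiring the ratings to come first.
- *The prompt is balanced.* It asks for limitations and difficulties as well as advantages. Correct, so no favourable direction of bias should be assumed.
- *An article condenses.* Section 2.9 mentions templates that are not shown, and arm-specific versions may exist. Against this, the article states positively who is asked, about what, and in which step.

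A reader might infer two stronger things. One is that a quarter of all questionnaires (10 of 40) would distort a pooled rating. Section 2.8 analyses groups within phases and pools no set of 40, so that share belongs to no planned analysis. The other is that correlated answers within discussion groups inflate the variance and make the tests too optimistic. The article gives neither a group size nor a correlation and does not establish group completion. An inflation factor for a single group mean also does not carry over to an arm difference, because an effect shared by both arms in a mixed group would cancel.

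**Conclusion.** The point holds as a risk of bias in the two secondary outcomes. It does not show that the results are contaminated. It rests on three stated facts: every participant enters sessions about the new device, Phase 2 arm B never uses it, and the questionnaire sits in the same step as the discussion. It affects the planned 10 arm B nurses through exposure, and all nurses through timing. Both readings of the rated object leave the Phase 2 comparison of satisfaction and intention of use hard to interpret. The amount and direction of bias are unknown, and the primary outcomes are untouched. The text should be changed before data collection, but the trial's main conclusions do not depend on it.

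**What to change.** Amend Table 2 and section 2.6, with one matching sentence in section 2.8:

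1. Each nurse completes the questionnaire individually, right after the last test procedure and before any interview or focus group.
2. Each nurse rates the syringe or syringes actually used: both types in Phase 1, the double-chamber syringe in Phase 2 arm A, and standard syringes in Phase 2 arm B. This keeps the planned within-phase comparisons. Dropping arm B from these outcomes altogether would delete the randomised Phase 2 comparison and should be avoided.
3. Summaries of double-chamber ratings include only nurses who used it (planned 30) and are shown by phase.
4. Arm B receives a prompt about the procedure it performed. Any comments it makes on the new device are reported separately as non-user opinion.

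The cost is one reordered session step and a second version of the prompt. Phase 1 nurses complete the questionnaire once per syringe type. If a single form was intended, that is 20 additional forms, or 20 × 42 = 840 item responses in total.
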